## Abstract

****Background**:**

There is evidence of a high prevalence of depression and anxiety in university students. Therefore, college time is a key period where prevention of mental disorders through interventions that promote resilience and mental health can be relevant. Currently, there are interventions available, but these are insufficient for those who need them. Online interventions are tools that can facilitate global accessibility and are easy for young people to use. CORE (Cultivating Our Resilience) is a self-administered online program, based on Ryff’s psychological well-being model, to promote resilience and coping skills in university students at risk of developing symptoms of depression or anxiety. The objective is to evaluate the effectiveness of this intervention protocol in comparison with an active control condition targeting healthy lifestyle, and a waiting list control condition. The study will be conducted in four populations of Spanish-speaking university students (Spain, Argentina, Colombia, and Mexico).

****Methods**:**

The study design is a randomized controlled trial (RCT). At least 324 university students will be randomly assigned to three conditions: 1) CORE, a 6-week training program to improve resilience; 2) HLP, a 6-week training to promote a healthy lifestyle; and 3) WL, waiting list control condition. The primary outcome measure will be the Connor-Davidson resilience scale. Additionally, measures of anxiety, depression, quality of life and socio-demographic variables (age, sex, incomes, marital status, among others) will be collected. Participants will be evaluated at pre-treatment, after each module, 6 weeks after allocation, and at 3-month follow-up. Intention-to-treat and per-protocol analyses will be performed.

****Discussion**:**

The results of this study will contribute to research on Internet-administered interventions and the implementation of a protocol that includes a series of components designed to improve resilience and coping skills, increase psychological well-being, and prevent depression and anxiety disorders in Spanish-speaking university students. In addition, avenues will be opened up for new research on the effectiveness of these interventions focused on the prevention and promotion of mental health in Spanish-speaking countries.

****Trial registration**:**

Registered at ClinicalTrials.gov NCT03903978 on April 2, 2019.

## Background

Depression is the leading cause of disability worldwide [1, 2]; globally, it is estimated that 4.4% of the population suffer from a depressive disorder, and 3.6% suffer from an anxiety disorder. According to the data, this prevalence is high in the European region with 12% for depression and 15% for anxiety, but even higher in the America with 14 and 21% respectively, predominantly in women than in men [3].. This impact is associated with lower quality of life and an increased risk of developing serious physical diseases [4], loss of health and functioning, with depression being one of the contributing factors to suicide at ages 15–29 [3, 5]. In light of the magnitude, improving the health of the population is only possible if the countries involved make prevention and treatment a public health priority [6, 7].

This preventive work should focus on at-risk populations and developmental stages of the disorders. Some of the most vulnerable stages include adolescence and early adulthood [8, 9] These stages correlate with higher rates of depression and anxiety in college students, compared to the adult population, according to data from recent reviews and meta-analyses [10–13].

College life is considered a stage with high stress factors and psychological distress [14, 15]. This vulnerability is associated with various stressors, such as lifestyle changes [16, 17] or cultural challenges [18] affecting personal relationships, academic and work performance [19–22], and quality of life related to physical and mental health [23]. These factors may increase the risk of developing a mental disorder [16] or lead to self-harming behaviours and even suicide [21, 24].

The university period is, therefore, a key environment for early detection and prevention of mental illness and increased personal well-being [13, 25]. A meta-analysis indicates that the interventions with the greatest effect for depression and anxiety in university students are cognitive behavioural therapy (CBT), mindfulness-based interventions and other interventions (such as art, exercise and peer support) [26]. Some studies have found a relationship between high levels of resilience and low levels of emotional disorders such as anxiety, depression, stress, and obsessive-compulsive disorder [27]. One of the preventive approaches to increasing psychological well-being is resilience [28], which promotes protective factors of adaptation to adversity, stress, and the negative effects of exposure to risk situations [29, 30]. These protective factors will moderate and reduce the impact of negative outcomes (such as prevalence of mental disorders) and promote positive outcomes (such as mental health or psychological well-being) [29, 31].

Based on this approach, several studies have demonstrated the effectiveness of resilience interventions in reducing depressive or anxious symptoms in youth, adolescents [32–35], and university students [36]. In addition, promoting resilience has been shown to be most effective with cognitive-behavioural interventions [32] combined with mindfulness techniques [37], improving personal relationships [38], coping strategies [39], and physical exercise [40] As a meta-analysis shows, work on protective factors rather than on other variables has a greater effect on promoting resilience [41]. However, there is still no empirically validated theoretical framework describing the mode of action of resilience interventions, and so it is important to study interventions that promote resilience and prevent stress-related mental health problems [42–44].

There are other lines of research focused on the prevention of mild or moderate depressive symptoms called low-intensity psychological interventions [45–47]. One of these interventions is the promotion of Healthy Lifestyles, which shows significant clinical benefits by promoting physical health, diet, and sleep control to reduce depressive symptoms [48], and it has also been proposed for interventions in college students to prevent risk behaviours [49–51]. Although this approach regulates risk behaviours, it can be an important factor in preventing emotional disturbance, and it can be compared to resilience-based interventions.

An effective technological tool for carrying out preventive and treatment interventions in mental health is the use of the Internet [52–55]. In Europe, 79% of the population between the ages of 16 and 74 use the Internet [56], and in Latin America and the Caribbean, 55% [57]. Mainly young people are immersed in the digital world, making the Internet an effective and efficient tool [58]. The Internet is, therefore, a valuable resource for implementing empirically validated prevention programs in different regions such as Europe and Latin America, which would reduce costs by facilitating access and meeting preventive mental health objectives in at-risk populations, as established by the World Health Organization [7].

Internet-based cognitive-behavioural treatments aimed at university students have been effective in reducing psychological stress, anxiety, and depression [59–61]. A meta-analysis points to this type of intervention as a feasible method to reach this population [62], and intervention protocols to promote resilience in university students have been published [36]. Internet-based interventions [63, 64] overcome barriers such as cost, availability of services, waiting time, access, and stigma. In addition, the same effectiveness has been demonstrated as in face-to-face interventions [65–68], whether or not they are preceded by a minimum amount of therapeutic care or with other mental health professionals [69–74], Thus, it is a feasible method for the prevention of mental disorders [75–77] and the promotion of healthy behaviours [58].

Online intervention is a growing field, given the increasing rates of access to technologies to people, the reducing on cost, and the potential advantages that this way of dispense the intervention provides (e.i. the scalability, overcoming geographical barriers, increasing in flexibility on time schedule …). Studies testing this kind of approach have been mainly conducting in developed countries with high or upper-middle incomes. Lately, efforts on testing the interventions in developing countries have been done. Protocols developed or validated on Western countries started to be adapted and tested [78–81] with different methodologies [82]. The evidence on the effects in countries with middle or low income are promising [79, 83, 84], but is still scarce [85]. One potential gap is the lack of resources to properly develop, adapt, and test the interventions. In this sense, the widespread use of Spanish language provides an opportunity to test already validated interventions in other countries with the need of minor changes. Therefore, the objective of the study is to test the effectiveness of an Internet-based preventive program to promote resilience and coping skills in college students at risk of developing emotional disorders in Spanish-speaking countries: Spain, Argentina, Colombia, and Mexico, compared to a healthy lifestyle program and a waiting list control group. The hypotheses are that the CORE program will improve the resilience, coping skills, and psychological well-being of college students. In addition, CORE and active control of Healthy Lifestyle are expected to be more effective than the Waiting List control group, but with greater and statistically significant effects of CORE as an intervention that is targeting to promote resilience.

## Methods/design

### Study design

A three-armed, single blind, randomized controlled trial (RCT) with repeated measurements at three times (at baseline, 6 weeks, and 3 months follow up) will be conducted in four Spanish-speaking countries (Spain, Argentina, Colombia, and Mexico). Due to the nature of the study, the condition will be notified to participants of to which they have been assigned, but those allocated to the intervention groups will remain unaware of the type of intervention they will receive. Participants who meet the inclusion criteria will be randomized to one of the three study arms in a 1:1:1 ratio: 1) unguided internet-based resilience intervention (CORE); 2) unguided healthy lifestyle program (HLP); and 3) Waiting list control (WL). Participants allocated to the WL condition will receive access to the intervention once they have completed the evaluation period.

The study has been approved by the Ethics Committee of University Jaume I in Spain, it was registered with the trial code NCT03903978, and it will be conducted in accordance with the CONSORT 2010 statement [86, 87], the CONSORT-EHEALTH guidelines [88], and the SPIRIT guidelines [89]. Figure 1 shows the study design.

**Fig. 1 Fig1:**
[figure not shown]
Study flowchart

### Sample size calculation

The primary outcome is the change in the resilience levels from baseline to post-intervention. Therefore, the Connor-Davidson Resilience Scale (CD-RISC) scores will be compared before and after the intervention in the CORE, HTP, and WL groups to obtain information about the normality of the CD-RISC scores within the target population. So far, there are no data on the effect size obtained for Internet-based interventions to promote resilience. However, a recent meta-analysis [37] compared the effectiveness of psychotherapy as an outcome for improving resilience in mental health and psychological well-being, and the authors found a moderate positive effect of resilience interventions (0.44, 95% CI 0.23 to 0.64). Considering these findings, the sample size was calculated with a significance level of 0.05, for a potency of 0.80. We take a conservative approach, we assume an effect of 0.5 (Hedges’ g), which, according to Cohen [90], can be considered a medium magnitude effect. Since our design included three experimental conditions (CORE, HLP, WL), one-way ANOVA was assumed for the statistical analyses. The total sample size calculated is 249 Estimating a potential dropout rate of 30%, the total sample size was determined to be 324, requiring 108 subjects in each condition [91].

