Consequently, the strengths of this study focus on two aspects: First, to our knowledge, this would be the first RCT to evaluate an online intervention to improve the resilience of Spanish-speaking college students (in Spain and Latin America). Second, CORE is a three-armed, single blind multi-country (Spain, Argentina, Colombia, and Mexico) randomized controlled trial (RCT) that will make it possible to study the generalization of the results in different Spanish-speaking students. Third, we are comparing the results with an active control, a rigorous Healthy Lifestyle program developed in Spain and characterized by the promotion of habits of physical health, diet, and sleep, that although outcomes analyses are in progress, preliminary data show acceptance and effectiveness of this low-intensity internet program to reduce the symptoms of depression [93]. However, this study has some limitations: first, dropout rates are expected to be high, as reported in previous research [144, 145]. For this reason, dropout rates have been taken into account in the calculation of the sample size. Second, Internet-based interventions for mental health also raise some ethical issues with regard to the exchange of data between Europe and America. For this reason, international guidelines will be followed to address these concerns [146, 147], as well as all aspects of Personal Data Protection under existing European legislation in compliance with General Data Protection Regulation 2016/679.

We consider that this study will provide future lines of research that will strengthen the implementation of these interventions. Little is known about the potential for cultural adaptation and the efficacy of interventions for mental disorders in low- and middle-income countries [148]. According to World Bank data, Colombia and Mexico are considered upper-middle-income countries and Argentina is a high-income country. However, the WHO includes them in America region, where the prevalence of mental disorders is higher than in the European region, but this variation may be due to the fact that many people have both conditions (comorbidity) and to the relatively larger populations between these two regions [5]. These data suggest the importance of prioritizing the prevention and treatment of mental disorders globally in both developing and developed regions [6].

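### The 30% dropout allowance was added as 249 × 1.30 = 324 instead of 249 / 0.70 = 356, so 324 covers only about 23% dropout

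*Protocol article*

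**What the plan says.** All the inputs are in the protocol article, under Sample size calculation.

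- Error rates: "the sample size was calculated with a significance level of 0.05, for a potency of 0.80".
- Effect: "We take a conservative approach, we assume an effect of 0.5", expressed as Hedges' g.
- Test: "one-way ANOVA was assumed for the statistical analyses", with three conditions.
- Requirement before dropout: "The total sample size calculated is 249".
- Requirement after dropout: "Estimating a potential dropout rate of 30%, the total sample size was determined to be 324, requiring 108 subjects in each condition".

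No inflation formula is written. The Abstract repeats the result as a minimum: "At least 324 university students will be randomly assigned to three conditions". The Discussion lists high expected dropout as a limitation and answers it by pointing to this calculation: "For this reason, dropout rates have been taken into account in the calculation of the sample size".

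**The concern.** A dropout rate is a fraction of those randomised. If 249 students must remain after 30% are lost, 249 is 70% of the number to randomise. Adding 30% of 249 on top of 249 takes the percentage of the wrong base and always gives too small a number.

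The stated combination of 249 needed, 30% lost and 324 randomised is therefore inconsistent. At the dropout rate the sponsor itself assumes, the trial ends below its own requirement and has less than the intended power for the primary outcome. This matters most when a non-significant result is read, in particular for CORE against the active healthy lifestyle control. The Discussion also tells readers that dropout has been provided for.

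**Working it through.** **Inputs from the article.** Total before dropout 249, i.e. 83 per arm with 1:1:1 allocation (Study design); dropout 30%; total after dropout 324, i.e. 108 per arm; alpha 0.05; power 0.80; effect 0.5; three arms.

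**1. Reproducing the stated figure.**

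- N × (1 + dropout): 249 × 1.30 = 323.7, rounded up to 324. Per arm, 83 × 1.30 = 107.9, rounded up to 108. Both match exactly.
- N / (1 − dropout): 249 / 0.70 = 355.7, rounded up to 356. Per arm, 83 / 0.70 = 118.6, rounded up to 119, giving 3 × 119 = 357 for equal arms. Neither matches.

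**2. What 324 delivers.**

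- Remaining at 30% dropout: 324 × 0.70 = 226.8, or 108 × 0.70 = 75.6 per arm.
- Shortfall: 249 − 226.8 = 22.2 students.
- Dropout at which exactly 249 remain: 1 − 249/324 = 0.231.

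**3. Power at the reduced number.** The article does not say how g = 0.5 was converted into an ANOVA effect, so power was computed in three ways that agree with 249:

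| Reading | Power at 249 (83 per arm) | Power at about 227 (75.6 per arm) |
|---|---|---|
| Omnibus F-test, effect f set so that 249 gives 0.80 (f = 0.198) | 0.800 | 0.759 |
| Tukey pairwise comparison, d = 0.5 | 0.805 | 0.762 |
| Two-sided t-test without adjustment, d = 0.44 | 0.805 | 0.767 |

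- The F-test uses the noncentral F distribution with 2 and N − 3 degrees of freedom and noncentrality N × f².
- The pairwise readings use a noncentral t with noncentrality d × √(n/2). For Tukey the critical value is the studentized range quantile divided by √2.
- The Tukey reading, which is the post hoc procedure under Statistical analysis, reproduces 83 per arm: 82 per arm gives 0.7998 and 83 gives 0.805.
- The t-test reading uses the meta-analytic estimate the article cites and also first reaches 0.80 at 83 per arm.

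**4. Check of the corrected number.** With 119 per arm and 30% lost, 119 × 0.70 = 83.3 per arm remain. Power for the Tukey comparison at d = 0.5 is then 0.807.

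**The case against.** **The power figure depends on where 249 came from.** A literal omnibus ANOVA does not reproduce it. The total for 80% power is 159 at f = 0.25, 177 at f = 0.236 (d = 0.5 between one arm and two equal arms) and 237 at f = 0.204 (d = 0.5 between the extreme arms, the third midway). At 227 students those effects give power of 0.928, 0.895 and 0.786. This stands as a limit on the 76%, which holds on the article's premise that 249 is the number for 80% power. The 22-student shortfall and the 23.1% tolerance do not depend on it.

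**Dropouts may not be wholly lost.** The intention-to-treat analysis uses mixed models with full-information maximum likelihood. Assessments are activated automatically, so a student who leaves the programme may still answer them. Baseline scores could also recover precision. Since 226.8/249 = 0.911, a baseline-adjusted analysis of 227 would match an unadjusted one of 249 if the pre–post correlation r satisfied 1 − r² = 0.911, so r of about 0.30. A change score would need 2(1 − r) = 0.911, so r of about 0.54. The article gives no correlation, so this shows only that the loss could be offset, not that it is. The size was justified by a one-way ANOVA, F-tests on post-test means are planned, and the sponsor inflated for dropout and so treated those students as lost. On those terms the inflation is wrong.

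**324 is only a minimum.** The Abstract does say at least 324, so recruitment may go higher. But it is the minimum that was miscalculated, and reaching it does not secure the stated design.

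**The loss is small.** About four points of power, no bias and no effect on type I error. This is fair, and it bears on how urgent the correction is, not on whether the statement is right.

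**Conclusion.** The error holds. The step from 249 to 324 multiplies by 1.30 where it should divide by 0.70, and nothing elsewhere in the article corrects it. From the article's own numbers alone, 324 tolerates 23.1% dropout, and 30% dropout leaves about 227 students against the 249 required.

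Power at 30% dropout is then about 0.76 instead of 0.80, so the type II error rises from 0.20 to about 0.24. That figure assumes that 249 corresponds to 80% power, as stated, and that students who drop out add nothing to the comparison, as in the one-way ANOVA used for sizing. The consequence is modest, but the sentence is wrong as written and the Discussion relies on it.

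**What to change.** Correct the sentence under Sample size calculation in one of these ways:

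- State that 324 randomised students allow for about 23% dropout while keeping the 249 required for 80% power.
- State that at 30% dropout 324 leaves about 227 students, with power of about 0.76 on the assumption that 249 gives 0.80.
- If the sponsor wants to keep both 30% dropout and 80% power, set the number to randomise at 357 (119 per arm).

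Either of the first two is sufficient. They need no further enrolment and no change of design; the only cost is a slightly less favourable tolerated dropout or power. The third needs 357 − 324 = 33 more students. The Abstract figure and the Discussion sentence on dropout should be brought into line with whichever is chosen.

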### Study population

The participants will be college students from Spain, Argentina, Colombia, and Mexico who score low on levels of resilience (−1SD) according to the primary outcome measure.

#### Eligibility criteria

Inclusion criteria will include the following: a) College students with a standard deviation score below the sample mean on the Connor-Davidson Resilience Scale (CDRISC-25). b) Adequate knowledge to understand and read and/or speak Spanish. (c) Internet access and computer skills.

Exclusion criteria include the following, college students: a) with a CMHD record in the past 12 months; b) who are or have been undergoing psychotherapy in the past 12 months; c) with a current or past psychotic or bipolar disorder; d) at risk of suicide.

Participants who do not meet the inclusion criteria will be provided with alternative interventions that are appropriate for their needs.

#### Recruitment

Five universities in Latin America and two in Spain were contacted. These partners contributed to the management of the ethical procedures in each of the countries and to the review of the procedures and contents of the interventions. The study will be announced on the official websites and e-mail addresses of the universities: Universitat Jaume I, Castellón, Spain, https://www.uji.es/; Universitat de Valencia, Spain, http://www.uv.es/; Universidad de Buenos Aires, http://www.uba.ar/; Universidad Nacional de Mar del Plata, Argentina, http://www.mdp.edu.ar/; Universidad Autónoma del Estado de Hidalgo, Mexico, https://www.uaeh.edu.mx/; Universidad Politécnica de Tecámac, México, http://uptecamac.edomex.gob.mx/; and Universidad Popular del Cesar, Colombia, https://www.unicesar.edu.co/. It will also be communicated through public spaces such as student social networks (e.g. Facebook, Instagram, and Twitter), posters, and newspaper advertisements. Interested students will request participation by email. A link with the informed consent and the screening criteria will be sent in reply.

